## TREATMENT INTERRUPTION

## Treatment interruption will be allowed for subjects who require temporary reduction or elimination of enteral nutrition due to intercurrent illness. The RELiZORB enzyme cartridge will continue to be used for any enteral nutrition that is administered during this time. Periods of intercurrent illness will be recorded on the adverse event form and addressed at the time of data analysis (see analysis section).

## SUBJECT DISCONTUNUATION

Subjects will be encouraged to complete the study; however, they may voluntarily withdraw at any time. The investigator will provide a written explanation of the reason for discontinuation in a source document, which will be transcribed to the appropriate CRF page. If a subject withdraws before completion, every effort will be made to complete the assessments scheduled during the final clinic visit.

A subject may be removed from the study for the reasons described in the sections below. Additionally, the subject will be removed from the study if any of the events described below (i.e., adverse event or intercurrent illness) result in a feed being withheld for more than 24 hours.

### Adverse Event

If a subject suffers an AE that, in the judgment of the investigator, the investigational product developer/distributer, or the DSMB presents an unacceptable consequence or risk to the subject, the subject may be discontinued from the study.

### Intercurrent Illness

A subject may be discontinued from the study if, in the judgment of the investigator, the subject develops an intercurrent illness or complication that is not consistent with the protocol requirements or that, in any way, justifies withdrawal from the study.

### Noncompliance

After the sponsor-investigator and study monitor consult (and Alcresta if appropriate), a subject may be discontinued from the study for the following administrative reasons:

- Failure to receive study device or treatment as mandated by the specific protocol.
- Failure to comply with protocol requirements
- Unauthorized, subject-initiated changes in dosing regimen

### Refusal of Investigational Product Administration

Any subject refusing clinical trial material for any reason will be discontinued from the study, and the reason(s) will be documented on the appropriate CRF. Reasonable efforts will be made to monitor the subject for AEs and to complete follow-up assessments after discontinuation. These efforts will be documented on the appropriate CRF page.

### Withdrawal of Consent

Any subject that withdraws consent for any reason at any time during the study will be discontinued from the study, and the reason(s) will be documented on the appropriate CRF.

## STOPPING RULES

If the sponsor-investigator, study monitor, or appropriate regulatory officials discover conditions due to reasons including but not limited to futility or risk(s) to the participants that arise during the study, the study should be paused or halted. This action may be taken after appropriate consultation among the sponsor-investigator, developer/distributer of the investigational product, , and DSMB. The trigger point for AE and study pause: Severity Level 3 and 4 AEs will be reviewed by PI and determined if it is worthy of study pause. Any change in stool that is higher than baseline will be discussed on a patient to patient basis.

## PREMATURE STUDY TERMINATION

If the sponsor-investigator, study monitor, or appropriate regulatory officials discover conditions arising during the study that indicate that the study should be halted, this action may be taken after appropriate consultation among the sponsor-investigator, developer/distributer of the investigational product, study monitor, and DSMB. Conditions that may warrant termination of the study include, but are not limited to, the following:

- The discovery of an unexpected, serious, or unacceptable risk to the subjects enrolled in the study
- A decision on the part of the developer/distributer of the investigational product to suspend or discontinue testing, evaluation, or development of the product.

A study may also warrant termination under the following conditions:

- Failure of the investigator to enroll subjects into the study at an acceptable rate
- Failure of the investigator to comply with pertinent regulations of appropriate regulatory authorities
- Submission of knowingly false information from the site to the Investigational Product developer/distributer, study monitor, or appropriate regulatory authority
- Insufficient adherence to protocol requirements

Study termination and follow-up will comply with the conditions set forth in the International Council on Harmonisation E6 Guideline for Good Clinical Practice, Sections 4.12, 4.13, 5.20, and 5.21.

# DATA COLLECTION AND PROCESSING AND STATISTICAL ANALYSIS

## DATA COLLECTION AND PROCESSING

Paper case report forms (CRFs) will be used to capture study assessments and data. The study coordinator or other delegated study personnel will enter data from source documents into the CRFs and then into the electronic database. The investigator will sign off on appropriate CRFs. Study documents related to consent, eligibility Unanticipated Adverse Device Effects (UADESs), and device accountability will be reviewed by the study monitor during periodic site visits. This can include consent forms, CRFs, study logs and source documents.

Training will be provided for the electronic data capture (EDC) system, InForm. All clinical trial personnel using the EDC system must have the necessary education, training, and experience or any combination of these. The investigator will be responsible for documenting employee education, training, and previous experience that pertain to the EDC system for all site personnel using the EDC system.

The investigator must maintain adequate security of the EDC system, including documentation that all users have been trained on the appropriate standard operating procedure and a list of authorized users. To ensure all data entries can be tracked, all personnel responsible for data entry must obtain InForm training certificates before any data can be entered in the database. The EDC system is configured to track all user entries and edits to the data.. Authorized study personnel will be assigned a unique password after receiving database training.

The sponsor-investigator must ensure that the electronic data systems are validated, and that data are backed up.

## STATISTICAL ANALYSIS

### General Overview

Data will be summarized in tables listing the number of subjects, mean, standard deviation, standard error, 95% confidence interval (CI), median, interquartile range (IQR), minimum, and maximum for continuous data and number of subjects, frequency and percentage for categorical data. Summaries will be presented by subject and visit, as well as in aggregate when appropriate. Outcomes will be presented in their native units (i.e. as collected), in addition to transformed units when necessary (for example logarithmic). Anthropometry outcomes (weight, height, head circumference, weight-for-height, body mass index) will be examined as z-scores using the Centers for Disease Control growth charts. All outcomes will be explored visually using various graphing methods, including (but not limited to) box-whisker, profile, and bar plots. All statistical analyses will be performed with SAS version 9.4 or later (Cary NC).

### Outcomes Evaluation

Continuous outcomes, which include all outcomes except the incidence of adverse events (AEs) and incidence of weaning from PN, will be described as indicated in the general overview above using summary measures at each visit. Incidence of ever weaning from PN will be summarized by frequency count and percentage. Analysis for incidence of AEs grade 2 or higher is described in the Safety Analysis section below.

Assessment of change in continuous outcomes will be made using the area under the curve between study day 7 and 90 (AUC_7-90_), adjusted for baseline, calculated over all relevant assessment timepoints (5 and 13 post-baseline weekly assessments for measurements obtained in clinic and at home, respectively). Measurements obtained in clinic will be assessed at study days 7, 14, 28, 60 and 90, while those obtained at home will be assessed on study days 7, 14, 21, 28, 35, 42, 49, 56, 63, 70, 77, 84, 90.

Adjustment for baseline will be made by dividing the outcome value at each assessment by the baseline value, leading to interpretation of AUC_7-90_ as a mean relative percent increase or decrease in outcome depending on whether AUC_7-90_ is greater or less than unity (1), respectively. AUC_7-90_ will be calculated as a time-weighted average, given by the equation:

$$\frac{0.5\cdot\sum\left( t_{i+1}-t_{i} \right)\left( r_{i}+r_{i+1} \right)}{\sum\left( t_{i+1}-t_{i} \right)}$$

where $t_{i}$ denotes the assessment day as described above,, and $r_{i}= y_{i}/y_{1}$ denotes the outcome at assessment day $t_{i}$ divided by the baseline (day 1) value. Hypothetical examples for a single subject with reduction in outcome at each visit is shown below in Figure 3 for measurements obtained in clinic (a) and measurements obtained at home (b). The dotted lines enclose a reference AUC_7-90_=1 (indicating no change in outcome), and the gray shaded area indicates AUC_7-90_.

Figure 3. Hypothetical examples of area under the curve for one subject

| [figure not shown] | [figure not shown] |
| --- | --- |
| a. Example of in-clinic outcome assessment. | b. Example of at-home outcome assessment. |

The assumption of normality will be assessed for AUC_7-90_ for each continuous outcome using quantile-quantile (Q-Q) plots and the Shapiro-Wilk test. Outcomes determined to be skewed will be normalized using an appropriate transformation (e.g. logarithm; normal scores based on ranks). AUC_7-90_ for each outcome will be summarized as described above in the General Overview section.

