| Clinical laboratory evaluations^d^ | X |  |  |  | X |  | X |  | X |
| Dietician Education | X |  | X |  | X |  | X |  | X |
| 72-hour fecal collection^e^ |  | X |  |  |  |  |  |  | X (final visit) |
| Lipid profile^f^ | X |  |  |  | X |  | X |  | X |
| Total plasma FAs^g^ | X |  |  |  | X |  | X |  | X |
| Liver tests^h^ | X |  |  |  | X |  | X |  | X |
| Nutritional assessment | X |  | X |  | X |  | X | Weekly | X |
| Record nutritional intake^i^ |  | Daily | X | Daily | X | Daily | X | Daily | X |
| Change in PN/ enteral feeding | X | X | X |  | X |  | X | Weekly | X |
| Home Body weight (WAZ) |  |  |  |  |  |  |  | Weekly |  |
| RELiZORB |  |  | X | Daily | X | Daily | X | Daily | X |
| Adverse Events^j^ |  |  | X | Daily | X | Daily | X | Daily | X |
| Concomitant Medications |  |  | X | Daily | X | Daily | X | Daily | X |
| Assess medical/ surgical procedures | X |  | X |  |  |  | X |  | X |
| Supply Investigational Product |  |  | X |  | X |  | X |  | X |
| Review Daily Patient Diary |  |  |  |  | X |  | X | Weekly | X |

I/E criteria = Inclusion and exclusion criteria.

FAs =fatty acids.

PN = Parenteral nutrition.

^a^ Record known bowel length/type from last surgical resection or other measurement.

^b^ Blood pressure, pulse rate, respiratory rate and temperature.

^c^ Includes height or length, head circumference (for subjects < 36 months), and weight. If a physical examination or nutrition assessment was performed during the 3-day screening period, it will be used for the baseline assessment when available.

^d^ Includes chemistry (including fat-soluble Vitamins A, D, E, and K), hematology, coagulation and C-reactive protein (CRP). Clinical laboratory evaluations obtained at time of screening will serve as the baseline assessment.

^e^ 72-hour fecal collection will occur in the 72 hours preceding treatment day 1 and the final clinic visit day 90

^f^ Samples of the lipid profile will include cholesterol, high-density lipoprotein (HDL), very low-density lipoprotein (VLDL), and low-density lipoprotein (LDL). Results of samples obtained at time of screening will be analyzed during enrollment period, prior to participant receiving device.

^g^ Samples of total plasma fatty acids will include total saturated, total monosaturated, total polyunsaturated, total Omega-3, total Omega 6, total fatty acids, a-linolenic Acid, linoleic acid, oleic acid, EPA, arachidonic acid, mead acid, DHA, and triene:tetraene ratio.

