### Safety Analysis

Safety analysis will be performed on all subjects enrolled in the study with a follow-up safety assessment. Adverse event data will be listed individually and summarized by system organ class and preferred terms within a system organ class. The number and percentage of subjects with adverse events (AEs), serious adverse events (SAEs), AEs that lead to discontinuation, study device-related AEs (determined by investigator), and AEs that lead to death will be summarized. Only AEs grade 2 or higher will be presented. When calculating the incidence of adverse events, each adverse event will be counted only once for a given subject. If the same adverse event occurs on multiple occasions in a subject, the occurrence with the highest severity and relationship to study device will be reported. If two or more adverse events are reported as a unit, the individual terms will be reported as separate events. AEs will also be summarized with regards to severity and relation to study drug. Additionally, the frequency of each AE within-subject will be calculated and summarized across all subjects in order to rank the commonality of each particular AE.

Vital signs, hematology, and clinical chemistry parameters from baseline to the end of the study will be presented as outlined above for continuous outcomes and reported to the DSMB at the regularly scheduled meetings. Incidence of changes in laboratory parameters from normal to abnormal, based on Boston Children’s Hospital reference ranges, will be identified and lab values listed by subject.

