A reliable estimate for the standard deviation (SD) of AUC_7-90_ for the primary outcome in this patient population is unavailable. Unpublished data for 7 patients are available, but at least 4 of these would not meet the eligibility criteria for this study (ages 1-10; 1 had a STEP procedure; 3 have pancreatic involvement). Nevertheless, the mean±SD reduction (AUC_7-90_) for these 7 patients was 0.81±0.14, representing a 19% decrease over 90 days. Using this SD with a sample size of n=32, a 20% observed reduction in outcome would provide a 95% confidence interval (CI) = (0.75, 0.85), ruling out a true mean population reduction smaller than 15%. Conservatively, if the SD was doubled (SD=0.28), the 95% CI = (0.7, 0.9), excluding a true mean population reduction smaller than 10%, our target threshold In general, for any continuous outcome, a sample size of n=32 with two-side alpha=0.05 will provide 80% power to detect an effect size (mean/SD) as small as 0.51, considered a medium-sized effect^25^.

Dichotomous outcomes and will be presented as proportions. The variance for a proportion (p) is at a maximum, and its CI at its widest, when p=0.50. Proportions farther from 0.50 (in either direction) have smaller variances, and hence narrower CIs. A range of proportions with 95% CIs for a sample of 32 subjects is provided; small: p=0.20 (0.06 – 0.34); medium: p=0.50 (0.33 – 0.67); and large: p=0.80 (0.66 – 0.94).

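### Dividing by one baseline reading puts the expected AUC7-90 above 1 when nothing has changed, so exploratory and laboratory outcomes with appreciable within-child variation lean towards an apparent increase

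*Protocol*

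**What the plan says.** Section 10.2.2 (Outcomes Evaluation) sets one method for nearly everything measured on a scale: "Continuous outcomes, which include all outcomes except the incidence of adverse events (AEs) and incidence of weaning from PN". The baseline step reads: "Adjustment for baseline will be made by dividing the outcome value at each assessment by the baseline value". In the formula each follow-up value is "divided by the baseline (day 1) value", the ratios are combined by the trapezoid rule into a time-weighted average, and the reference line at 1 is described as "indicating no change in outcome". Values above or below 1 support an "interpretation of AUC_7-90_ as a mean relative percent increase or decrease in outcome".

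Section 10.2.3 (Safety Analysis) extends the method: "Vital signs, hematology, and clinical chemistry parameters from baseline to the end of the study will be presented as outlined above for continuous outcomes". For laboratory values the denominator is a single draw. A footnote to Table 2 says: "Clinical laboratory evaluations obtained at time of screening will serve as the baseline assessment".

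Section 10.2.1 asks for the mean, standard error, 95% confidence interval and median, among other summaries. At the end of section 10.2.2, an AUC judged skewed from Q-Q plots and the Shapiro-Wilk test is to be transformed, for example by logarithm or by normal scores of ranks. Section 10.2.5 (Sample Size) adds an inferential claim for all such outcomes: "In general, for any continuous outcome, a sample size of n=32 with two-side alpha=0.05 will provide 80% power".

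**The concern.** A ratio with a noisy denominator does not average to 1 when the true level is constant. A child whose baseline happens to read low gains more on the ratio scale than a child whose baseline reads high by the same amount loses. More follow-up visits do not help, because the error sits in the denominator that all of a child's ratios share. For an outcome that is always positive, the error points upwards.

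The trial has no control arm in which the same drift would show. A confidence interval lying above 1 for a variable plasma fatty acid or fat-soluble vitamin could therefore be taken as evidence of better absorption, and the same artefact could appear as a rise in a variable safety laboratory value reported to the DSMB.

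**Working it through.** **The protocol's own figures.** With n = 32 and t(0.975, 31) = 2.04, the interval is 0.80 ± 2.04 × SD/√32. SD 0.14 gives 0.7495 to 0.8505, and SD 0.28 gives 0.699 to 0.901. One-sample power at effect size 0.51 is 79.8%. All agree with section 10.2.5. The sample-size arithmetic is right; the question is what the AUC estimates.

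**Expected ratio under no change.** Let a child's true level be μ, with independent errors at baseline and follow-up. Then E[y_i/y_1] = μ × E[1/y_1], which exceeds 1 because 1/y is convex. For lognormal error with s² = ln(1 + CV²), E[1/y_1] = exp(s²)/μ, so the expected ratio is exactly 1 + CV². Any weighted average of such ratios has the same expectation.

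**Simulation.** 4,000 trials per setting, 32 children, no true change, lognormal within-child error, and the protocol's trapezoid weights. For clinic days 7, 14, 28, 60 and 90 the weights are 3.5/83, 10.5/83, 23/83, 31/83 and 15/83, that is 0.042, 0.127, 0.277, 0.373 and 0.181. The home schedule has 13 assessments. The CV is assumed, because the protocol states none.

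| CV | 1 + CV² | Mean AUC, clinic | 95% CI wholly above 1, clinic | 95% CI wholly above 1, home |
|---|---|---|---|---|
| 5% | 1.0025 | 1.0025 | 3.7% | 4.1% |
| 10% | 1.01 | 1.009 | 5.1% | 6.3% |
| 20% | 1.04 | 1.039 | 12.2% | 15.1% |
| 30% | 1.09 | 1.090 | 22.1% | 29.0% |
| 40% | 1.16 | 1.160 | 33.6% | 41.7% |
| 50% | 1.25 | 1.251 | 48.3% | 58.5% |

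The nominal figure is 2.5%. The interval lies wholly below 1 in at most 1.6% of trials, falling to about 0%. A second run of the clinic schedule gave 6, 12, 22 and 47% at CV 10, 20, 30 and 50%. Additive normal error gives a similar picture: mean AUC 1.047 and 11.3% above 1 at CV 20%.

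**Does the transformation step cure it?** Only in part, because the log is taken after the arithmetic averaging. With every AUC logged, the geometric mean at CV 20, 30 and 50% is 1.014, 1.031 and 1.083 (clinic) and 1.018, 1.044 and 1.109 (home). The interval is wholly above 1 in 5.5, 7.0 and 12.3% (clinic) and 6.9, 12.0 and 20.8% (home). The step is also conditional: on the clinic schedule Shapiro-Wilk rejects in about 24% of trials at CV 20% and 43% at CV 30%. If that test alone decides, about 11, 17 and 20% of trials still show a false increase at CV 20, 30 and 50%. Normal scores of ranks leave no reference value of 1 to compare with. The median AUC is also shifted, to about 1.03 (clinic) and 1.045 (home) at CV 30%.

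**Alternatives on the same data.**
- Time-averaging log(y_i/y_1) within child gives a geometric ratio of 0.999 to 1.003, with 2 to 3% of intervals beyond the null on each side.
- The ratio of group means (time-weighted follow-up mean over baseline mean) gives 1.000 to 1.010.
- Keeping the AUC but using a three-day mean baseline (home schedule) gives 1.013, 1.030 and 1.083 at CV 20, 30 and 50%. Against 1.040, 1.094 and 1.252 with one day, the excess falls to about a third (0.013/0.040, 0.030/0.094, 0.083/0.252).

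**The case against.** The strongest reply concerns certainty and scope, and much of it stands.

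- **Size.** The title outcomes could be read as all showing false increases. The protocol does not support that: it gives no within-child CV, and nothing ties 40 or 50% to any listed outcome. Vital signs and tightly regulated chemistry may well sit where the bias is trivial. Positive correlation between baseline and follow-up error would shrink it further.
- **Testing.** A reader might infer a formal one-sample test against 1. None is named; section 10.2.2 says the AUC will be summarised, and the sample size is called precision-based. What remains is that 95% intervals are to be read against 1, and section 10.2.5 claims a two-sided alpha and power for any continuous outcome.
- **Safeguards.** Section 10.2.1 also asks for native-unit summaries by visit, which ratio averaging does not touch. Q-Q plots may prompt a log more often than Shapiro-Wilk alone. Section 10.2.3 adds normal-to-abnormal laboratory changes, which do not use the ratio. These soften the problem without correcting the AUC.
- **Intake.** Entry requires an unchanged enteral formula and rate for a month, so enteral intake is partly protected. Oral intake has no such criterion.
- **A spurious pattern of benefit.** It is tempting to say that many fatty acids rising together would pass for a consistent device effect. But the panel includes mead acid and the triene:tetraene ratio, and the protocol does not call a rise in these favourable. These outcomes are also exploratory.

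**Conclusion.** The point holds for positive outcomes with appreciable within-child variation: some plasma fatty acids and vitamins, variable laboratory values, and possibly oral intake. For these, 1 is the wrong reference for a mean of individual ratios to one reading. The excess is about CV², which rests on independent errors and an assumed CV: negligible at 5 to 10%, material from about 20% upwards.

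A reader might infer that the primary result is at risk. It is not. For PN calories the bias pushes the AUC up, against showing a reduction, and should be small if PN is stable at entry (less than a 5% reduction over at least a month, although investigator discretion is allowed). A true ratio of 0.80 would be expected to read 0.80 × 1.0025 = 0.802 at CV 5%, or 0.80 × 1.01 = 0.808 at CV 10%.

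**What to change.** 1. For strictly positive laboratory and fatty-acid outcomes, including vitamins, time-average log(y_i/y_1) within child with the existing weights, compare with 0, and report the geometric mean ratio with its 95% confidence interval. Do this in all cases, not only when the AUC looks skewed.
2. For oral and enteral intake, which can be zero, report the ratio of the time-weighted follow-up mean to the baseline mean with a bootstrap interval. Alternatively, keep the AUC and use the mean of the intake already recorded on Days -3 to -1 as the denominator; this cuts the bias to about a third but does not remove it. State which intake record is the baseline.
3. Keep AUC7-90 for PN calories, so that the pilot value, precision statement and 10% threshold in section 10.2.5 still apply. Add the ratio of means as a sensitivity analysis only, since it gives more weight to children with high PN intake.

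The cost is wording and a small program change, with no new data or visits. Estimates for the affected outcomes become geometric or group-level ratios instead of means of individual percentages, and apparent increases become somewhat smaller.

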### Secondary efficacy endpoint

The secondary efficacy endpoint is the change in body weight (weight-for-age z-score) since baseline, assessed weekly throughout the study.

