### Exploratory endpoints

- Change in 72-hour fecal fat composition and coefficient of fat absorption from enrollment, assessed at Days -3 to -1, to Days 87-89.
- Change in plasma serum fatty acid profile, and fat-soluble vitamins (A, D, E, and K) from baseline, assessed at Day 7, 14, 28, 60, and 90.
- Change in height (height-for-age z-score) and head circumference (head-circumference-for-age z-score) [in subjects < 36 months]) from baseline, assessed at Day 7, 14, 28, 60, and 90.
- Change in BMI z-score from baseline, assessed at Day 7, 14, 28, 60 and 90.
- Change in PN volume from baseline, assessed weekly.
- Change in enteral nutrition tolerance (calories and volume) from baseline, assessed weekly.
- Change in oral nutrition tolerance (calories and volume) from baseline, assessed weekly.
- Ability to wean from PN, assessed over the entire course of the study.

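### Dividing by baseline does not work for z-scores: the secondary endpoint changes direction in children with a negative baseline and is unstable near zero

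*Protocol*

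**What the plan says.** Section 3.3.2 states: "The secondary efficacy endpoint is the change in body weight (weight-for-age z-score) since baseline, assessed weekly throughout the study". Section 10.2.1 puts all growth measures on that scale: "Anthropometry outcomes (weight, height, head circumference, weight-for-height, body mass index) will be examined as z-scores using the Centers for Disease Control growth charts". Section 3.3.4 lists height, head circumference (under 36 months) and BMI z-scores as exploratory endpoints, together with "Change in oral nutrition tolerance (calories and volume) from baseline, assessed weekly".

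Section 10.2.2 then sets one method of assessing change for "Continuous outcomes, which include all outcomes except the incidence of adverse events (AEs) and incidence of weaning from PN". The baseline step is: "Adjustment for baseline will be made by dividing the outcome value at each assessment by the baseline value". The ratios r_i = y_i/y_1 are averaged over time from Day 7 to Day 90, and the result is read as a "mean relative percent increase or decrease in outcome depending on whether AUC_7-90_ is greater or less than unity (1), respectively". The Statistical methods part of the synopsis repeats the rule.

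Section 10.2.4 keeps 1 as the no-change value when the first or last visit is missing. It also defines the best- and worse-case imputations by distance from 1. Nowhere does the protocol exempt z-scores, offer a difference-based version, or say what to do with a zero or negative baseline.

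**The concern.** A ratio to baseline means something only when zero is a true zero and the baseline is positive. A z-score of 0 is the reference average, and values below it are negative. Dividing by a negative baseline turns a gain into a ratio below 1 and a loss into a ratio above 1. A baseline close to 0 makes the ratio very large in either direction. The inclusion criteria in section 3.2.1 do not restrict baseline z-score, so all of these cases can arise.

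At stake is the stated measure of change for the only secondary efficacy endpoint and for three exploratory growth endpoints. Averaging over children whose ratios point in opposite directions gives a number with no interpretation.

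Oral calories and volume have a related problem. No eligibility criterion requires oral intake, so a child may have a baseline of 0, and the ratio then cannot be formed.

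**Working it through.** **The plan's own figures.** Section 10.2.5 plans precision for the PN-calorie AUC at n = 32. With half-width t(0.975, 31) × SD/√32 around 0.80, SD 0.14 gives (0.750, 0.850) and SD 0.28 gives (0.699, 0.901). Both agree with the protocol. They concern PN calories, and the protocol gives no comparable figure for a z-score.

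**Formula for a z-score.** Inputs are the at-home assessment days in section 10.2.2 (7, 14, …, 84, 90), baseline b on Day 1, and a linear path reaching b + g on Day 90 (the linear path is an assumption):

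- z(t) = b + g(t − 1)/89
- The trapezoid average of t over Days 7 to 90 is 48.5, so the average of (t − 1)/89 is 47.5/89 = 0.534.
- Ratio AUC = 1 + 0.534 × g/b
- Time-weighted average of the difference z(t) − b = 0.534 × g

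The ratio AUC depends on g/b. When b is negative, its departure from 1 has the opposite sign to the gain.

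**Single children.**

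| Baseline b | Change g by Day 90 | Ratio AUC | Plan's reading | Average difference |
|---|---|---|---|---|
| -2 | +1 | 0.73 | 27% decrease | +0.534 |
| -2 | -0.5 | 1.13 | 13% increase | -0.267 |
| -2 | +0.2 | 0.95 | decrease | +0.107 |
| -1 | +0.2 | 0.89 | decrease | +0.107 |
| -0.1 | +0.2 | -0.07 | decrease of more than 100% | +0.107 |
| +0.1 | +0.2 | 2.07 | increase of more than 100% | +0.107 |
| +1 | +0.2 | 1.11 | increase | +0.107 |
| 0 | any non-zero | undefined | none | 0.534 × g |

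The same gain of 0.2 z thus gives five different ratio results, three in the wrong direction, but one value on the difference scale.

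**Whole trials.** Assumptions: n = 32, baseline SD 1, gain by Day 90 ~ N(0.2, 0.15), linear paths, no measurement error, 20,000 simulated trials per row. The mean baseline is varied because the documents give none.

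| Mean baseline z | Trials with mean AUC below 1 despite a true mean gain |
|---|---|
| -1.5 | about 84% |
| -0.8 | about 69% |
| -0.5 | about 62% |
| 0 | about 50% |
| +0.5 | about 38% |

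A second set of 4,000 trials per row gave every child a true gain of 0.3 z and added measurement noise. The shares were 82%, 70%, 58% and 45% at mean baselines of -1.5, -1, -0.5 and 0. The median SD of the AUC in those trials was 0.43 to 1.35.

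**Do the plan's transformations help?** Section 10.2.2 offers a logarithm or rank-based normal scores for skewed AUCs. The logarithm does not exist for a negative AUC, and at a mean baseline of -0.8 about two thirds of trials contain at least one. Ranks preserve the ordering, so the reversed children stay reversed. Medians do not help either: at -0.8 the trial median is below 1 in more than 99% of trials.

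**The case against.** The strongest reply is that the harm is limited.

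- **Native-unit summaries.** Sections 10.2.1 and 10.2.2 require summaries at each visit in native units, and section 10.2.1 adds plots. A rise in mean z-score would be visible there. This stands as mitigation. But section 10.2.2 makes the ratio AUC the assessment of change, so the report could carry two results that disagree in direction.
- **A wide interval rather than a firm wrong result.** At a mean baseline of -0.8, the 95% confidence interval lies wholly below 1 in only about 12% of trials. This also stands. The usual product is an uninformative interval, which is still no use for a secondary endpoint.
- **The analysis plan could settle it.** The protocol does not leave the point open. It fixes a formula and its reading, and an analysis plan that used differences would contradict it.

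Some stronger readings are tempting but unsupported:

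- A reader might infer that catch-up growth would always be reported as a decrease. Reversal needs a negative baseline. At positive baselines the direction is right and only the size is arbitrary.
- A reader might take a move from -2 to -1 as a reported 50% decrease. That is the ratio at one visit. The plan interprets the average over Days 7 to 90, which is 0.73 on a linear path.
- A reader might call the ratio undefined near 0. It is undefined only at exactly 0 and unstable close to it.

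**Conclusion.** The point holds. As written, the ratio rule gives the wrong direction for any child with a negative baseline z-score, unstable values near 0 and no value at 0. It affects weight-for-age z-score and the three exploratory z-scores, though head circumference concerns only children under 36 months. The single-child results follow from the formula and a linear path.

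The trial-level shares, about 84% down to 38%, rest on assumed baselines and gains and should be read as a range. They do not show that this trial will report weight loss, because its baseline z-scores are unknown.

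The primary outcome should not be drawn into this. At least 30% of calories must come from PN at entry, so baseline PN calories are positive and the ratio is meaningful. For oral calories and volume the defect is division by zero in any child with no oral intake at baseline.

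**What to change.** 1. In section 10.2.2 and the synopsis, define change for all z-score outcomes, and for oral calories and volume, as the time-weighted average of y_i − y_1 over the same days, with 0 as no change.
2. Keep the ratio, with 1 as no change, for outcomes that are strictly positive at baseline. PN and enteral calories and volume qualify through the entry criteria. State the scale for each remaining continuous outcome, including laboratory values, vital signs, plasma fatty acids, vitamins, fecal fat and the coefficient of fat absorption.
3. In section 10.2.4, for the difference-scale outcomes, restate around 0 both the no-change value of AUC_F-L and the best- and worse-case imputations.

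The cost is an edit to three places in the protocol: the synopsis and sections 10.2.2 and 10.2.4. Visits, measurements and sample size do not change, and no new data are needed.
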